## Protocol overview

With current knowledge, it is difficult to set a randomized trial between a population undergoing VT-ART (e.g., in the compassionate setting often applied for patients proposed for such an innovative procedure) and a population not undergone to that. Randomizing a patient’s accrual to VT-ART instead of the conventional option implies that some patients would skip a conventional procedure in favor of a procedure still considerate at least still non-standard, although promising. Multiple, reliable phase I and phase II trials are not available, although case series and at least one phase I/II trial have investigated VT-ART efficacy (1).

Finally, it would be difficult to define two balanced treatment arms that are suitable for a clinical randomized comparison, since patients undergoing VT-ART would have either already received RFA or are unable to receive it, and they have already undergone other standard treatments. On the other hand, setting a single-arm trial would test less efficiently the clinical of VT-ART and could imply the adoption of VT-ART only for worse clinical case presentations.

This multicenter observational study will evaluate the efficacy and safety of VT-ART. Our trial will enroll patients with optimized medical therapy, in whom endocardial and/or epicardial RFA is either unfeasible or fails to control VT recurrence. The trial is set as observational since it indirectly comparing VT-ART with a conventional procedure (i.e., RFA).

Each patient recruited for VT-ART will be profiled according to a predefined list of characteristics that will be circulated within the centers participating to the consortium to collect other patients with a similar profile, not having undergone VT-ART, for final analysis.

The peculiar setting of our trial will avoid precluding VT-ART to patients possibly taking advantage of such a therapeutic option; moreover, it will compare VT-ART with retrospective series not having receive VT-ART anyway. Furthermore, this approach will retrieve otherwise sporadic data about single or limiter case series of each center joining the consortium. This trial is not strictly investigational but can add notable scientific information to the current scenario.

The multicenter setting of this study will allow for faster recruitment of the sample size.

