## Populations

Our aim is to enroll patients with structural heart disease, in whom the presence of a myocardial scar induces refractory monomorphic VT or ventricular fibrillation (VF), as documented by either implantable cardioverter defibrillator (ICD) appropriate shocks or anti-tachycardia pacing (ATP) at ICD interrogation. We will enroll patients with recurrent VT/VF episodes despite optimal medical therapy (i.e., class III antiarrhythmic drugs) and at least one previous attempt of RFA or patients in whom ablation is not feasible, because of contraindications to the procedure or of patient intolerance. Previous percutaneous stellate ganglion blockade is neither a requirement for inclusion criteria nor exclusive criteria that will be collected in the standardized data collection for potential subgroup analysis.

Eligibility criteria are summarized in Table 1.

**TABLE 1 T1:** Inclusion and exclusion criteria.

Inclusion criteria	1. Patients with structural heart disease and monomorphic VT refractory to optimal medical therapy and previous RFA attempts (minimum of one attempt RFA)
	2. Patients with contraindications to conventional ablation or not suitable for any non-interventional approach, refusing any surgical ablative attempt; or patients who have already undergone RFA with arrhythmogenic focus refractory to previous ablation procedures
	3. Age >18 years
	4. Candidates not suitable for heart transplantation

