## Methods/design

Our trial will investigate the effects of administering a single fraction of external beam radiation delivered through SBRT techniques at a dose of 25 Gy on patients with recurrent episodes of VT and in whom optimal medical therapy and previous RFA attempts have failed to provide benefit from VT burden control. We will perform matched pair analysis with dynamic cohorts. We will compare two groups of patients: One that has been treated by all the standard approaches but has not undergone VT-ART and a second group that has also received VT-ART. The entire enrolled group (by multicentric recruitment) will be stratified according to some predefined characteristics and analyzed by matched pair analysis, based on the characteristics of patients treated with VT-ART. Once a patient is enrolled to undergo VT-ART within the multicentric consortium, the search for two patients with similar feature profiles not undergoing VT-ART will be shared.

Matching factors taken into account are summarized in Table 2.

**TABLE 2 T2:** Applied matching factors.

Parameter type	Subgroup options
Etiology of cardiomyopathy*	ICM
	NICM
	ACM
Age*	
Gender*	
BMI	
LVEF*	
NYHA group*	
Ventricular arrhythmia presentations*	Sustained ventricular tachycardia incessant sustained ventricular tachycardia electrical storm
Arrhythmogenic focus anatomical intracardiac location	Based on VE exit by ECG and by the activation map of VT
Diagnostic tools used for scar definition	CT
	MR
	EAM
	ECG
TA volume*	Endocardial electroanatomic substrate mapping area/volume in all cases; epicardial mapping area/volume in the case of 3D epicardial electroanatomic substrate mapping
Heart volume	cc range
Heart-to-TA volume	cc range
Previous use of amiodaron	Y/N
Number of previous RFA attempts*	
Type of previous RFA attempts	endocardial
	epicardial
Unfeasibility to repeat RFA	Y/N
Local recurrence of TA (same area of last RFA)	Y/N
Previous percutaneous stellate ganglion blockade	Y/N

TA, target area by electroanatomical mapping; BMI, body mass index; RFA, radiofrequency ablation; LVEF, left ventricle ejecting fraction; *mandatory matching factor.

Figure 1 depicts the design of the VT-ART study.

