## Outcome measures

The primary outcome is investigating the difference in overall cardiovascular survival among the group undergoing VT-ART and the one not exposed to the innovative procedure.

The primary efficacy endpoint is a statistically significant difference in overall cardiovascular survival between the group undergoing VT-ART and the one not exposed to the innovative procedure; this will be defined in months and calculated from the time of the last procedure (represented by the last RFA for the control group and VT-ART for the innovative one, respectively).

The secondary outcome is evaluating the difference in ventricular event-free (referred to VT/VF, appropriate shock or ATP as recorded by the ICD) survival after the last procedure between the two groups (i.e., the single or last RFA in the control group and VT-ART in the innovative group). The respective endpoint is a statistically significant difference in ventricular event-free survival (in months) after the last procedure between the two groups.

An additional secondary aim is to evaluate the reduction in the number of VT episodes compared to the pre-treatment period between the two dynamic cohorts that will be investigated.

Ventricular tachycardia recurrence will be defined as evidence of monomorphic VT at ICD interrogation (either self-limiting or terminated by appropriate shock therapy or ATP). The number of VT episodes, defined as VT burden, in the 3 months before and after the procedure will then be compared.

The respective secondary endpoint will be evaluated facing 3 months before the last procedure (i.e., either RFA or VT-ART) and 3 months after.

We did set a blanking period after VT-ART before evaluate the effect on VT burden; in a recent study by Kautzner et al., the authors supported the pre-clinical theorem of myocardial apoptosis (up to 3 months post-stereotactic ablation) followed by a creation of fibrotic lesion (6–9 months post-stereotactic ablation) in the irradiated region (5). Consequently, we propose a 3-month-blanking period after the procedure.

Since a blanking period of 3 months after the procedure will be applied, the secondary endpoint will evaluate the number of VT episodes interval accounted for the last 3 months before the procedure and of the 3–6 months after it.

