#### Sample size

The calculation of the sample size considered followed assumptions:

-A total of 95% confidence level;-The drop-out rate of 10%;-Expected difference between the two treatments for 3-month and 6-month VT burden in terms of overall response rates: 20% higher in arm including VT-ART compared to the control group;-Power of 80%.

To improve clinically adequate balancing, we will enroll two matching paired patients in the group not undergoing VT-ART for each patient who undergoes VT-ART in a 2:1 ratio, favoring a larger proportion of patients not undergoing the innovative procedure (i.e., VT-ART).

Under these hypotheses, to detect a 20% improvement in the VT burden control rate in the VT-ART group vs. the control group, we calculated the sample size (in a 2:1 ratio) upon enrolling 149 patients: 100 in the non-exposed control group and 49 in the VT-ART group. Progressively, on a multicentric basis supervised by the promoting center in the VT-ART consortium, for each VT-ART patient enrollment, a matched pair patient profile according to the predefined features will be shared with the consortium to enroll two similar patients who have not undergone VT-ART. For enrollment into the control group, recruitment of clinical cases from retrospective case series within the multicentric consortium will also be allowed, with the only condition to be not earlier than 5 years from the enrollment of the matched pair patient in the VT-ART group (to avoid the possible influence of a too early approach for standard procedures).

All statistical analyses will be performed using SPSS^®^ version 25.0 software (©Copyright IBM Corporation 1994, 2017).

Due to the potential difficulty of enrolling the patients through the complete match of all matching factors, a protocol rule will be applied through patient’s collection.

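### The matching omits the pre-procedure VT count, which is the baseline of the VT-burden endpoint, so differential regression to the mean can create or hide a group difference

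*Protocol article*

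**What the plan says.** - **Endpoint.** Under Outcome measures, an additional secondary aim is to "evaluate the reduction in the number of VT episodes compared to the pre-treatment period between the two dynamic cohorts". Burden is a count: "The number of VT episodes, defined as VT burden, in the 3 months before and after the procedure will then be compared". After introducing a 3-month blanking period, the section settles the windows: "the secondary endpoint will evaluate the number of VT episodes interval accounted for the last 3 months before the procedure", against months 3 to 6 after it.
- **Index procedure.** For the survival endpoint, time zero is the last procedure, "represented by the last RFA for the control group and VT-ART for the innovative one, respectively". The VT-burden windows also run from the last procedure, either RFA or VT-ART.
- **Entry.** Populations describes one condition for the study population: "We will enroll patients with recurrent VT/VF episodes despite optimal medical therapy", with a previous RFA or RFA not feasible.
- **Matching.** Methods/design states: "Matching factors taken into account are summarized in Table 2". The statistical section repeats the list with some additions. If accrual of controls is slow, matching falls back to the mandatory factors. None of the three sets contains a VT count. The nearest item, which is mandatory, is arrhythmia presentation: sustained VT, incessant sustained VT or electrical storm.
- **Sizing.** The 149 patients (100 controls, 49 VT-ART) rest on a VT-burden response rate "20% higher in arm including VT-ART compared to the control group".

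**The concern.** In a non-randomised comparison, matching has to do the work of balancing the groups. Here it covers BMI, heart volume and the imaging tool used to define the scar, but not the starting value of the outcome being compared. Counts can differ many-fold within one presentation category.

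VT burden fluctuates. A patient whose pre-procedure window happens to be high will tend to show a fall afterwards without any treatment effect. If one group is selected more strongly on recent burden than the other, it regresses more, and the difference looks like a treatment effect, or cancels one. The matching profile drives enrolment of controls, so an analysis plan written later cannot restore matching on a variable that was not used. The sample size also rests on VT-burden control, so this is the outcome that the study is sized to detect.

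**Working it through.** **1. The plan's own figure.** Inputs from Sample size: 95% confidence (two-sided assumed), 80% power, a difference of 20% (read as 20 percentage points), 2:1 allocation, 10% drop-out. With k = 2 controls per VT-ART patient and pooled proportion p̄:

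n(VT-ART) = [1.96·√((1 + 1/k)·p̄(1 − p̄)) + 0.8416·√(p₁(1 − p₁) + p₀(1 − p₀)/k)]² / 0.20²

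No control rate is given, so 149 cannot be reproduced uniquely. A rate of 10% vs 30% gives 44 + 88, and after division by 0.90, 49 + 98 = 147. A rate of 72% vs 92% gives 45 + 90, then 50 + 100 = 150. The point does not depend on this figure; the 20-point effect serves only as a yardstick.

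**2. Absolute scale.** The protocol does not say whether reduction is absolute or proportional. With the same 75% fall in both groups and assumed starting counts of 20 and 10, the absolute reductions are 0.75 × 20 = 15.0 and 0.75 × 10 = 7.5. The apparent advantage of 7.5 episodes comes from the baseline alone. The proportional falls are equal.

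**3. Response rate with no treatment effect.** Assumptions: patient rate 4·exp(0.8·Z) per 3 months; the count in each window is Poisson with that rate times an independent lognormal period effect of mean 1 and log-SD s; response is a fall of at least 50% (the protocol defines no threshold); 400,000 patients.

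| Pre-procedure count | Response, s = 0.8 | Response, s = 1.2 |
|---|---|---|
| at least 1 | 40.4% | 49.6% |
| at least 3 | 46.7% | 59.1% |
| at least 6 | 54.2% | 67.8% |
| at least 10 | 60.5% | 74.1% |

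- Extreme pairing, at least 10 vs at least 1: 60.5 − 40.4 = 20.1 and 74.1 − 49.6 = 24.5 points. If the period effects are not centred at mean 1, the gap is 18 to 21 points.
- Moderate pairing, at least 6 vs at least 3: 54.2 − 46.7 = 7.5 and 67.8 − 59.1 = 8.7 points.
- Selection that rises smoothly with the pre-procedure count: a false gap of 10 to 13 points, which falls to 2 to 3 points once controls are matched in bands of 1–2, 3–9 and 10 or more.
- Same selection in both groups: no gap.

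**4. False-positive rate.** 49 vs 100 patients, burden on a standardised log scale, no true effect, 4,000 runs per setting. The groups differ by d SD through selection on the pre-procedure value; ρ is the pre/post correlation (both assumed). The unadjusted change shows a spurious extra fall of (1 − ρ)·d. For d = 0.5:

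| ρ | Spurious fall | False positives, change score | False positives, adjusted for baseline |
|---|---|---|---|
| 0.3 | 0.35 SD | 38% | about 5% |
| 0.5 | 0.25 SD | 30% | about 5% |
| 0.7 | 0.15 SD | 21% | about 5% |

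Over d = 0.25 to 0.75 the change score gives 9% to 71%.

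**5. Where the remedy fails.**
- *Stable difference.* Let VT-ART patients have twice the long-run rate, with no treatment effect and a pre-procedure count of at least 1. In the model of step 3 their response rate is lower: 34.8 vs 40.4% (s = 0.8) and 43.9 vs 49.6% (s = 1.2), about 6 points. Matching in the bands raises the control figures to 45.7% and 54.6%, so the false gap against VT-ART widens to about 11 points. On the log scale (d = 0.5, ρ = 0.5) the change score is unbiased, while baseline adjustment is biased by −0.25 SD.
- *Treatment at a transient peak* of 0.5 SD (ρ = 0.5). Adjustment lowers the spurious effect from 0.50 to 0.25 SD and false positives from 81% to 36%, not to 5%.

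**The case against.** **The bias need not favour VT-ART.** A reader might infer that VT-ART patients are referred when their count is high. Protocol overview says only "in the compassionate setting often applied for patients proposed for such an innovative procedure", which concerns neither the count nor its timing. Both groups have recurrent VT, and the controls' pre-procedure window also precedes an intervention for VT. Regression to the mean therefore occurs in both, and only a differential part biases the comparison. This stands: the direction is unknown.

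**The analysis may be adjusted.** A reader might infer an unadjusted comparison from the chi-square, t-test and non-parametric tests named. The protocol fixes no model for this endpoint, and a separate analysis plan could add a covariate. This also stands, so the firm part of the point is the matching.

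**Presentation is already matched.** It is a mandatory proxy and makes an extreme imbalance less plausible. It narrows the imbalance in count but does not remove it.

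**Baseline matching or adjustment can itself bias.** True, as step 5 shows. That argues for a sensitivity analysis, not for ignoring the baseline.

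**The endpoint is secondary.** The primary is cardiovascular survival. The sample size nevertheless rests on VT-burden control.

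**Conclusion.** The omission is in the text: no matching set contains the pre-procedure 3-month VT count, although that count is the baseline of the endpoint. If the groups differ in it through selection on recent burden, the comparison can be distorted in either direction. The false response gap is roughly 8 to 13 points for moderate imbalance, that is, 40% to 65% of the planned 20 points (8/20 and 13/20). A false gap as large as the planned effect might be inferred, but it needs one group made up of patients with 10 or more episodes set against one with 1 or more, which nothing in the protocol suggests. All these sizes rest on assumed rates, variability and a 50% response threshold, since the protocol supplies none of them. With no differential selection and no stable difference between the groups, this bias does not arise.

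**What to change.** 1. In Table 2 and in the list in the statistical section, add the ICD-recorded number of VT episodes in the 3 months before the procedure as a mandatory matching factor, in broad bands (for example 1–2, 3–9, 10 or more, with a stated rule for a count of zero).
2. State that the months 3 to 6 count is compared between groups as a rate ratio adjusted for the log pre-procedure count (for example by a negative binomial model), respecting the matched sets.
3. Report pre-procedure counts by group, and give the change-from-baseline comparison as a sensitivity analysis, because matching or adjustment can bias the result if the groups differ stably in long-run burden. Conflicting results should be reported as such.

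**Cost.** One table row and two or three sentences; the count is already needed for the endpoint. One more mandatory factor makes matching somewhat harder, in a scheme that already foresees difficulty and performs no final analysis below a 1:1 ratio. If accrual suffers, keep the adjustment and the sensitivity analysis and drop the matching row.

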Other secondary objectives include identifying the benefits of VT-ART on cardiac function, as evaluated through an electrocardiogram, echocardiographic, biochemical variables, and patient’s quality of life.

In particular, we will evaluate the reduction or suspension of antiarrhythmic drug use compared to the baseline and the improvement of cardiac parameters (such as LVEF, left ventricular end-diastolic volume/diameter, ventricular strain, end-systolic volume/diameter, RVEF, and TAPSE for right ventricular function).

Analyzed biochemical variables will include heart failure biomarkers, such as NT-proB-type natriuretic peptide (NTproBNP), troponin (hs-TnI), and inflammation markers, such as polymerase chain reaction (PCR), tumor necrosis factor-alpha (TNF-alpha), and interleukin 6 (IL-6).

Improvement in the patient’s quality of life will be assessed compared to the pre-treatment period using the SF36 scale.

The patient’s QoL will be assessed before and after VT-ART using the SF36 scale (6); the post-treatment score will be compared to the pre-treatment period’s one to assess potential improvement. The post-treatment QoL evaluation will be performed at 3, 6, and 12 months after VT-ART. Once centers join the consortium, the SF36 QoL scale will be offered (although not mandatory) to all patients undergoing RFA: Before and at 6 months after conventional therapy.

Secondary outcome analyses will investigate the improvement of QoL scores after VT-ART and how QoL scores change the comparison between VT-ART and RFA.

Further secondary outcome analyses will be developed through imaging: Contrast infusion MRI and CT scan will be performed as required but not mandatory (if not contraindicated due to ICD) in the experimental arm.

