### Statistical considerations and sample size for matched pair analysis

A descriptive analysis will summarize the total number and stratification of patients with RFA and VT-ART.

We will perform a comparative analysis between RFA and VT-ART in patients with structural heart disease and refractory VT. Each patient who will be treated by VT-ART will be compared with two patients in the control group treated with RFA and best standard care but without VT-ART, on the basis of the following matching factors: Etiology of cardiomiopathy (ICM, NICM, and ACM), ventricular arrhythmia presentations (sustained ventricular tachycardia; incessant sustained ventricular tachycardia; and electrical storm), diagnostic tools used for scar definition (CT, MR, EAM, and ECG), arrhythmogenic focus anatomical intracardiac location (on the basis of VE exit by ECG and by activation map of VT), TA volume (endocardial electroanatomic substrate mapping area/volume in all cases; and epicardial mapping area/volume in case of 3D epicardial electroanatomic substrate mapping), heart volume, heart-to-TA volume, rate number of previous RFA attempts, type of previous RFA attempts (endocardial and epicardial), time (in days) between the first RFA attempt and VT-ART, time (in days) between the last RFA attempt and VT-ART, previous percutaneous stellate ganglion blockade, time (in days) between the percutaneous stellate ganglion blockade and VT-ART previous use of amiodaron, NYHA group, LVEF, BMI, age, and gender.

As mentioned, applied matching factors are summarized in Table 2.

Continuous data will be expressed as mean ± standard deviation, as appropriate, for all variables collected from the entire population or specific subgroups. A comparative analysis for subsequent levels of qualitative variables through the chi-square test and quantitative variables (scores on quality of life) with the *T*-test will be performed.

Non-parametric tests will be provided where the population distribution does not have a known form (normal Gaussian).

The differences in baseline and follow-ups between the same group will be analyzed with repeated measures approach: using the Friedman test and MANOVA for continuous variables and McNemar or Cochran’s *Q*-tests for categorical ones.

The significance of the tests is fixed with *p* < 0.05.

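### Antiarrhythmic-drug reduction is framed as a benefit of VT-ART but judged against each patient's own baseline, and nothing commits it to the matched-control comparison

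*Protocol article*

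**What the plan says.** In the protocol article, Outcome measures introduces a group of further secondary objectives: "Other secondary objectives include identifying the benefits of VT-ART on cardiac function". For drug treatment it then specifies that "we will evaluate the reduction or suspension of antiarrhythmic drug use compared to the baseline". No test, coding or comparison group is named in that sentence.

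The statistical considerations section sets a general rule: "The differences in baseline and follow-ups between the same group will be analyzed with repeated measures approach". Under that rule, categorical variables are assigned to McNemar or Cochran's Q, at p < 0.05. The same section also states "We will perform a comparative analysis between RFA and VT-ART in patients with structural heart disease and refractory VT" and plans "A comparative analysis for subsequent levels of qualitative variables through the chi-square test". Neither of these last two statements names drug use.

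On drug status at entry, Populations says: "We will enroll patients with recurrent VT/VF episodes despite optimal medical therapy (i.e., class III antiarrhythmic drugs".

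**The concern.** The question is whether VT-ART lowers the need for antiarrhythmic drugs. A comparison with the patient's own baseline answers a different question: whether drug use changed. Intolerance, toxicity, switching or down-titration after any procedure would all count towards the result. The matched controls exist to show how often such changes happen without VT-ART.

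Elsewhere, Outcome measures says when it wants the two groups compared. The reduction in VT episodes is to be compared between the two cohorts, and quality of life gets an added VT-ART versus RFA comparison. Drug use gets no such clause. Read naturally, the within-group rule then applies, and a significant p-value could be published as a benefit of VT-ART without the controls having been consulted.

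**Working it through.** The article states no figure for this endpoint, so there is none to reproduce.

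**Inputs from the article.** 49 VT-ART patients and 100 controls; 10% drop-out, so 49 × 0.9 ≈ 44 evaluable if 49 is taken as the number before drop-out; significance at p < 0.05 (taken as two-sided).

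**Assumed, because the article does not give it.** The background rate r of reduction or suspension unrelated to VT-ART, varied from 5% to 20%.

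**Step 1: coding as worded (reduced or suspended, yes/no).** Every baseline value is no, so all b discordant pairs point the same way. Exact McNemar gives p = 2 × (1/2)^b:
- b = 5: 2/32 = 0.0625
- b = 6: 2/64 = 0.031

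The threshold is therefore 6 of 49 (12.2%), or 6 of 44 (13.6%), whatever the cause of the change.

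**Step 2: chance of reaching 6 with no VT-ART effect.** Pr(X ≥ 6) with X ~ Binomial(n, r):

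| r | n = 49 | n = 44 | controls, n = 100 |
|---|---|---|---|
| 5% | 3.5% | 2.2% | 38% |
| 10% | 37% | 27% | 94% |
| 15% | 76% | 66% | 99.8% |
| 20% | 95% | 90% | about 100% |

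At r = 12% and n = 49 the probability is 54%, so false significance becomes more likely than not from about there. The last column shows that the same test would find a significant reduction in the RFA group even more readily.

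**Step 3: Cochran's Q with baseline and three follow-ups.** The result depends on when changes occur. If they are present from the first follow-up, simulated rejection is about 89% at r = 10% and 98% at 15%. If they accumulate at a constant hazard, it is about 76% and 96%.

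**Step 4: other codings, McNemar, n = 49, r = 5/10/15/20%.**
- On/off drug, 95% on drug at baseline, 10% of the others starting: 2.3/27/64/87%.
- On/off drug, 90% on drug, 10% of the others starting: 1.5/20/52/78%.
- On/off drug, 90% on drug, 50% of the others starting: 0.3/4.6/17/37%.
- Reduced versus increased, equally likely (10-30% each): 1.1-1.5% in the favourable direction, so the test holds its level.

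The shares on drug and the start rates are assumptions; the article gives neither.

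**Step 5: comparison with controls.** A chi-square test of 49 versus 100 with the same background rate in both groups (10-30%) rejects in 4.9-5.1%. Fisher's test on 49 versus 98 (5-30%) rejects in 3-4%.

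**The case against.** No sentence assigns McNemar or Cochran's Q to drug use. The rule is generic, and the same section plans an RFA versus VT-ART comparison and a chi-square test for qualitative variables. A chi-square test on the proportion reduced or suspended would fit that text. Coding, time point and the test for each endpoint are also matters that an article commonly leaves to the full protocol or analysis plan. All of this stands, and the absence of those details is not the point made here.

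Three stronger readings are tempting and not supported:
- **That the plan definitely tests this endpoint within group and excludes the controls.** This follows only from combining two sections, and a controlled analysis is not ruled out.
- **That a symmetric null is impossible.** This depends on entering a change variable with an all-no baseline. On/off status, number of drugs or dose level would each have a real baseline, and a reduced-versus-increased coding holds its level.
- **That ordinary drug changes make a significant result near certain.** This depends on an unknown background rate. At 5% the error is 3.5%, below nominal.

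The objection does not rescue the attribution. Under any coding, a change from own baseline mixes an effect of VT-ART with everything else that alters prescribing. Holding the nominal level under one coding does not turn the within-group null into a null about VT-ART.

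**Conclusion.** The point holds in a limited form. The article frames drug reduction as a benefit of VT-ART, sets the patient's own baseline as the comparator, and offers only a within-group test for a categorical change of that kind. It does not commit the endpoint to the controls that the design collects. A within-group result could not be credited to VT-ART.

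The size of the error is conditional. Coded as worded, 6 changes among 49 patients suffice. The false-positive probability then runs from 3.5% to 95% over assumed background rates of 5% to 20% (2.2% to 90% with 44 evaluable). On/off coding gives lower figures, and how much lower depends on the share on drug at entry and the start rate among the rest.

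This concerns one minor secondary objective. The primary endpoint, the main secondary endpoints and the sample size are not affected.

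**What to change.** In Outcome measures and the statistical considerations, state that inference on antiarrhythmic reduction or suspension rests on VT-ART versus matched controls. Define the endpoint as the proportion reduced or suspended at 6 and 12 months after the index procedure (VT-ART, or the last RFA in controls). Analyse it by matched set, with conditional logistic regression or Mantel-Haenszel, and report the difference with its 95% CI. Report the within-VT-ART proportion with an exact CI, and with no p-value read as benefit.

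The cost is a change of wording plus abstraction of drug status for controls. That abstraction is not free: the follow-up list in the article does not include drug status, controls may be retrospective, and prospective RFA patients follow the schedule only where possible. Some control data will be missing and should be reported as such. The interval will also be wider than that of a one-group test.
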